**Subject Compliance**

We will assess subject compliance with the study in 3 ways: a), From information downloaded from the meter on every 3rd day, (b), Dossette, (c), Contact with parents. There will be 2 criteria for compliance: (i) at least 6 distinct data downloads from the meter every month; and, (ii) less than 25% residual pills in the dossette at each visit.

g. Is any aspect of this research study being conducted in the Medical School or a non-UMMMC facility? If yes, please explain.

No.

h. Will hospitalization be required as part of this research study?

| Yes |  | No | X |
| --- | --- | --- | --- |

If yes, how long will subjects be hospitalized?

i. Will there be any material inducements or recruitment incentives given to research staff or research subjects as part of this research study? (e.g., direct payments, free hospitalization, care)

| YesX |  | No |  |
| --- | --- | --- | --- |

If yes, explain how much, the pay schedule, or any partial payments that will be given.

Each participant will receive $120 for the entire study. This payment will be made at the rate of $20 per visit for the 6 visits. This money will be issued as a gift card to a bookstore at each of the 6 visits.

*The committee is exceedingly sensitive to the threat of coercion that can stem from excessive compensation for participation in research. The IRB recommends hourly payments of $20/hr for every hour (or fraction thereof) the subject is involved in the study. This should include time in the hospital or clinic that is solely for the study, travel time, and time spent recovering from a procedure or an anesthetic agent used for a procedure. Time that the subject is unable to perform his/her routine activities of daily living due to study related issues should be included in this time. (Time required to perform multiple minor tasks should be lumped together; that is, filling out a questionnaire that takes 15 minutes on four different days constitutes one hour of labor, not four hours.) If reimbursed, cost of transportation ($0.35/mile), parking and meals should be noted. A bonus of up to $50 may be given for completion of a long term study or for studies that involve low risk but uncomfortable procedures (such as endoscopy, multiple blood samples for pharmacokinetic studies, gynecological examinations, etc).*

1. **DISCLOSURE OF CONFLICT OF INTEREST**

Investigators should disclose any financial arrangement they may have with a company whose product figures prominently in their research or financial arrangements they may have with company making a competing product. **The relationship should also be described in the informed consent documents**. In the case where the only relationship is that a company is sponsoring the research study, it is sufficient to prominently identify the sponsor on the front page of the consent form and to simply state “NONE” in the consent form under Conflict of Interest.

Is there a conflict of interest?

| Yes |  | No | X |
| --- | --- | --- | --- |

**6. RELATIONSHIP TO STANDARD THERAPY.**

Describe the standard therapy that patients would receive if not in the research study. Explain how this research intervention deviates from or replaces generally accepted standard therapy and justify the deviation.

Standard Treatment for Double Diabetes:

There is no consensus on the modalities of treatment for double diabetes in children and adolescents. Most endocrinologists would treat these individuals with insulin only. However, recent reports[43] now suggest that overweight adolescents with type 1 diabetes who are going through puberty would benefit from adjunctive therapy with agents that counteract the insulin resistance brought on by increased adiposity. Other studies have shown that patients with type 2 diabetes who possess diabetes-associated autoantibodies lose their beta cells faster than those without autoantibodies and thus will be dependent on insulin therapy sooner. Therefore, our study does not deviate from the emerging method of treating patients with double diabetes. Even though we cannot say that treat-to-target regimen is standard of care in children, the blood glucose targets we are using for age are defined by the American Diabetes Association. The only difference is that we have a dedicated staff that will follow up with the family to ensure compliance with the guidelines. Determir and aspart are standard of care.

RESEARCH INTERVENTION STUDY:

Eligible candidates will be required to receive either placebo or metformin 1000 mg daily. The follow up schedule and monitoring regimen are the same for other patients with diabetes.

The Research Study Protocol deviates from the Standard management of Double Diabetes:

- Quarterly blood draws for lipids, leptin, adiponectin, serum creatinine, hepatic function tests and 25OHD. The standard of care for blood draws is yearly blood draw for lipids, thyroid function tests, celiac antibodies, 25OHD, and quarterly blood draws for HbA1c.

**7. DESCRIBE THE POTENTIAL BENEFITS OF THIS PROJECT.**

1. Include hoped-for benefit to society, to the group of subjects or to individual subjects.
2. Address the risk/benefit ratio of the study. If there are no direct subject benefits, this should be stated.

Benefit to Society:

This study will help to determine the efficacy of metformin therapy in reducing both A1c levels and body mass index in patients with double diabetes. It is our hope that the findings from this study would help in the development of new treatment regimen for double diabetes.

Benefit to subjects:

Subjects may benefit directly by experiencing an improvement in their glycemic control, which might translate to a reduction in their risk of diabetes complications. Those randomized to metformin arm of the trial may also benefit from the mild weight loss effect of metformin.

Risk/Benefit ratio of the study:

Apart from the initial blood draw for screening tests and subsequent blood draws every 3 mo for lipids, leptin, adiponectin, A1c, and 25OHD, the study has the same level of risk as the standard therapy for double diabetes. The risk benefit ratio is very low, i.e., the subjects are not subjected to any additional risk other than what they would experience during a standard treatment for double diabetes. Metformin therapy is generally safe and is widely used in the treatment of type 2 diabetes and polycystic ovarian syndrome in children and adolescents. It is the only oral drug approved by the Food and Drug Administration for use in the management of diabetes in children.

**8. DESCRIBE THE POTENTIAL RISKS TO SUBJECTS INCLUDE PSYCHOLOGICAL, ECONOMIC, LEGAL OR SOCIAL RISKS AS WELL AS PHYSICAL RISKS.**

**Include the following information:**

a. Estimate likelihood of occurrence, severity, and duration. If generally accepted quantitative estimates are available based on previous data, these should be stated. Otherwise, qualitative estimates such as “rare”, “occasionally", or “frequently” may be used. *The committee needs scientific information about drug/device side effects so as to best judge the pros and cons of the study.* ***Do not simply cut and paste the consent form “Risk” section into this part of the protocol.***

Risks associated with study procedure:

Some children and adolescents may become embarrassed when given a physical examination or asked detailed questions about their diabetes. Some may be bothered by having blood drawn due to fear of needles or concern about pain. A numbing cream used to minimize pain can cause a slight swelling at the application site. There is a minor risk of infection at the site of the needle stick. In about 1 in 20 cases, a child may faint or become sick to the stomach at the sight of a needle or when blood is drawn. There may be some discomfort or bruising at the site of the needle stick. To alleviate the pain of needle stick, EMLA cream will be provided for subjects who wish to numb the site of blood draw before the needle stick.

Risks associated with medications:

1. Metformin: As a result of participating in this study, subjects randomized to the metformin arm will receive metformin 1000 mg once daily by mouth for 9 months. This dose is within the range of normal starting dose of metformin for pediatric patients with either diabetes or polycystic ovarian syndrome. Common side effects associated with metformin therapy include nausea, loss of appetite, diarrhea, gas, and a metallic taste. These usually subside with time and do not necessitate discontinuing the medication. Lactic acidosis is a rare but potentially serious side effect that is more likely to occur in individuals with heart, kidney, or liver failure. Lactic acidosis is very rare in children with diabetes.
2. Insulin: Hypoglycemia is a recognized risk of insulin therapy. However, all our participants would have been on insulin therapy for at least 6 months prior to being enrolled in our study. Thus, they have the knowledge and skills to recognize and manage hypoglycemia. We will also conduct a session on our titration regimen during the Run-in phase to familiarize participants with the protocol and possible side effects such as hypoglycemia.

Treat to target regimen and oral medications will not be initiated simultaneously. Our protocol is to initiate and familiarize the patients with all aspects of treat to target regimen during the run-in phase of the study without adding metformin or placebo. Thereafter, we will introduce the oral agents. Therefore, subjects will have ample time to work with treat to target regimen before receiving oral agents.

We do not anticipate an increased frequency or risk of hypoglycemia with the treat to target regimen because treat to target regimen is not a unidirectional model of care. It is based on a bidirectional flexible model that allows the patient to subtract or add 1-2 units to his/her long acting insulin dose depending on his 3-day average fasting blood glucose level. We have also built in a close follow up and monitoring plan for this study. For example, the frequent phone calls during which we will review finger stick blood glucose readings with the family and the fact that the families will fax or email finger stick blood glucose readings to us twice weekly will ensure very close monitoring of blood glucose excursions throughout the study duration. We will also ensure that participants maintain a bedtime blood glucose level of >100 mg/dL before going to sleep. Participants will also check 3AM blood glucose twice weekly and also on 2 consecutive nights following changes to their long-acting insulin dose. We will also instruct the families to call the diabetes line during the first week of treat to target regimen if any fingerstick blood glucose reading is <70 mg/dL or two readings of >250 mg/dL.

We also do not anticipate the adjunctive metformin therapy to cause hypoglycemia as we will be titrating basal insulin doses to the prevailing glycemia, and will reduce the dose of basal insulin if there is evidence of incipient hypoglycemia.

Finally, we have included a Hypoglycemia Monitoring Table to enable participants document their low sugar reactions in an effective way so we can address these reactions promptly.

b. Explain what steps will be taken to protect against its occurrence, minimizing the harm, methods for early detection of harm, and what procedures will be followed to avoid serious injury (e.g. withdraw from study or dose reduction).

Study Safety Officer: [name].

As the safety officer [name] will monitor participants in the study for adverse events related to the study drug, and make recommendations regarding removing subjects from the study or terminating the study if the incidence of adverse effects is significant.

He will review unblinded study data every month for the first 3 months of the study, and then every three months thereafter with regards to assignment of subjects to the study arms, prevalence of gastrointestinal side effects (including nausea, diarrhea and abdominal discomfort), unusual weight loss (>10% of body weight in 3 months), admissions to hospital or elevation of liver enzymes to >3 times above the normal limit. He will also review all other SAEs. This information will be forwarded to him by the study coordinator, and unblinding information by Investigational Drug Services which is responsible for blinding the study drug. He will perform this review every 3 months until the completion of the study. If an issue is found, he will report this promptly to the PI and will jointly issue an adverse effects or SAE report (as the case may be) with the PI to the UMass IRB and the study sponsor, Novo Nordisk Inc.

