**4. DETAILED DESCRIPTION OF RESEARCH PLAN (especially as it affects the subject)**

1. Include a schematic representation of what the research will entail (e.g. a table with the number of visits and what will happen at each visit or flow diagram of subject’s involvement over time).

Table 1. Schematic Representation of the Study Protocol for Trial of optimized Insulin-Metformin Therapy

| Procedure | Visit I  (-3mo): Start of Run-in period +  screening  Duration: 1hr | Visit II (-2 mo)  Run-in period+ | Visit III (month 0)  Baseline study visit: Duration 1hr | Visit IV (month +3)  Interim study visit:  Duration 30 min | Visit V (month +6)  Interim study visit;  Duration 30 min | Visit VI  (month +9)  Study conclusion  Duration:1hr |
| --- | --- | --- | --- | --- | --- | --- |
| History and Physical Exam | X | X | X | X | X | X |
| Nutrition Counseling |  | X | X | X | X |  |
| Instructions on treat-to-target regimen | X | X | X | X | X |  |
| Research Blood draw |  |  | X | X | X | X |
| Urine collection | X |  |  |  |  | X |
| Screening labs  (part of research lab draw) | X |  |  |  |  |  |
| Run in phase | X | X |  |  |  |  |
| Implementation of Treat-to-target regimen | X | X | X | X | X |  |
| Metformin/Placebo |  |  | X | X | X |  |
| Review of blood glucose data and insulin dose adjustments | X | X | X | X | X | X |

Trial design:

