This will be followed by close monitoring of blood glucose levels in the first 2 weeks on standard aspart and detemir regimen to ensure normoglycemia. Parents will be advised to fax a copy of their child’s **glucose log book** in the first 2 weeks for our review and recommendation of insulin dose adjustment if necessary. All subjects will continue to use their personal log books and logging techniques. All participants will return to the clinic at the end of one month (from the time of starting on standard aspart and detemir regimen) for a comprehensive review of glycemic management.

At the end of the 3-month run-in period, all participants will continue on treat-to-target insulin regimen, and will then be randomized to either of the 2 arms of the study: **an experimental arm**, consisting of treat-to-target insulin regimen plus metformin, and **a control arm** consisting of treat-to-target insulin regimen plus placebo. Both the physicians and patients will be blinded to the oral agents being administered to patients.

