**Summary of Procedure:**

This research study involves 6 visits: two screening visits and 4 study visits. Subjects who meet the inclusion criteria will be invited to enroll in the study. **Consent** will be obtained from subject’s parents or guardian. Participants who are 10-17 years of age will give assent; and participants who are 16 and 17 years of age will sign the parental consent form along with their parents. Subjects will undergo a 3-month **run-in period** to screen for complications, to update patient education, and to assess subject’s compliance with study protocol. To **screen for complications** of therapy, we will review patients’ history of frequency and severity of hypoglycemic events. Patients with a history of severe hypoglycemia (<30 mg/dL) on more than 3 occasions in the preceding month will have to be closely monitored. Specifically, we will review each episode of severe hypoglycemia immediately after the event to determine the cause. Common causes include overinsulinization, administering the wrong type of insulin, skipping meals, and unexpected strenuous exercise. If our review detects any of these common causes, we will instruct the family on how to prevent future occurrences and monitor the patient’s glucose logs every 3 days for any repeat hypoglycemic events. If our review did not detect any of these causes, then we will recommend that the candidate be withdrawn from the study.

Patients with hypoglycemia unawareness will only be enrolled after they have regained the ability to recognize hypoglycemic events. This is easily achieved by allowing these individuals to main slightly elevated blood glucose levels for a period of 2 weeks. Patients will be placed on detemir and aspart with no adjunctive metformin or placebo during the run-in period. All participants will be instructed on the treat-to-target regimen and be given a **summary sheet** to familiarize themselves with the regimen. Treat-to-target regimen will only commence at the end of the run-in phase.

*Consent:*

After the investigator explains the study and answers all questions, 10-15 year old participants who agree to participate will sign an assent form, 16-18 year old participants who agree to participate will sign an informed consent form, and a parent of the 10-17 year old participants will provide permission by signing the informed consent form.

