**Procedure**

Following the blood draw, each subject will be started on a patient-directed, treat-to-target insulin regimen. All participants will be on multiple daily injections (MDI) consisting of once daily injection of long acting insulin analog, detemir, meal time insulin boluses with aspart, and a correction factor for insulin to ensure euglycemia between meals. All insulins will be administered using a flexpen device. For this study we will confirm the adequacy of each aspect of therapy by an ongoing monitoring system as described by Bode et al[59], and summarized below. We will use a ‘teach back’ protocol to ensure that patients understand the bolus insulin adjustment and correction factor plan.

Our goal for the participants is to maintain their blood glucose levels as shown below in the Table 2.

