**Table 3. Supplemental Insulin Dose Adjustment Plan**

| Prior meal Blood Glucose levels (mg/dL) | Current meal blood glucose level (mg/dL) | Supplemental Insulin dose (SID) |
| --- | --- | --- |
| greater than 130 | 80-130 | Interpretation: correct SID  Instruction: nothing to do |
| greater than 130 | less than 80 | Interpretation: SID is too high  Instruction: increase sensitivity factor by 10 |
| greater than 130 | greater than 130 | Interpretation: SID is too small  Instruction: decrease sensitivity factor by 10 |

**C. Basal Insulin adjustment plan:** Basal detemir injection will be given consistently at bedtime once a day. Subjects will titrate their long-acting insulin analog (detemir) dose every third day, to achieve a fasting plasma glucose of 90-120 mg/dL using the algorithm shown in Table 2 below. We will aim to maintain participants on a total daily **basal** insulin dose of 0.3-0.8 U/kg/day or higher if necessary, given once daily at bedtime. This will ensure relative normal inter-prandial glycemia and the achievement of our HbA1c targets.

**D. Metformin or Placebo:** All participants will be provided with a 3 month supply of metformin or placebo at baseline, +3, and +6mo. Subjects will be advised to start at one capsule daily for 2 weeks, and then increase to 2 capsules once daily for the remainder of the study duration.

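### The protocol starts treat-to-target insulin both in the run-in and at month 0: its safety assurance needs the first, its standard-therapy reference period the second

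*Protocol*

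**What the plan says.** **Start during the run-in.** Section 8a (risks associated with medications) says that "Treat to target regimen and oral medications will not be initiated simultaneously" and that "Our protocol is to initiate and familiarize the patients with all aspects of treat to target regimen during the run-in phase", with the oral agents introduced afterwards. It concludes that "subjects will have ample time to work with treat to target regimen before receiving oral agents". Two other places agree:

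- Table 1 in section 4a has the row "Implementation of Treat-to-target regimen | X | X | X | X | X". The first two marks are Visit I (−3 months) and Visit II (−2 months).
- The trial design text says that when the run-in ends "all participants will continue on treat-to-target insulin regimen" and are then randomized.

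**Start at month 0.** The Run-in Phase paragraph, the run-in item that follows the Summary of Procedure, and the Visit I procedures all describe a change to detemir and aspart with treat-to-target held back. The Summary of Procedure, and again the Protocol paragraph in section 4f, state: "Treat-to-target regimen will only commence at the end of the run-in phase". The Visit III (month 0) procedure states: "Following the blood draw, each subject will be started on a patient-directed, treat-to-target insulin regimen".

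**Study drug.** Item D, Metformin or Placebo, says: "All participants will be provided with a 3 month supply of metformin or placebo at baseline, +3, and +6mo". Table 1 marks metformin/placebo from Visit III onward and not before.

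**Analyses that depend on the timing.** Secondary Aim 1 identifies the run-in with standard insulin therapy and follows HbA1c as patients move from it to treat-to-target with the same two insulins. H1D compares mean HbA1c at −3 and 0 months in all patients with later values in the placebo group.

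**The concern.** Site staff cannot follow both Table 1 and the visit procedures. Two things turn on which one they follow.

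The first is a safety statement. Section 8a offers the ethics board, for a trial mainly in minors, a staggered introduction of insulin titration and oral drug. The assessments for safety name hypoglycemia as the major concern. If the visit procedures are what happens, that statement is wrong.

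The second is what the month-0 HbA1c represents. It is either the value after three months of standard aspart and detemir, or a value already changed by up to three months of titration. Secondary Aim 1 and H1D read it as the former.

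**Working it through.** The point rests on no statistical calculation, and the sample-size figures do not enter it. The check dates the two interventions under each version and sees which statements survive.

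**Step 1. When does the study drug start?** The oral agent is supplied at baseline, +3 and +6 months, 3 months at a time: 3 × 3 = 9 months of supply. Section 8a gives 9 months of metformin, and the statistical section gives an intervention period of 9 months. The study ends at +9 months, so dosing begins at about 9 − 9 = month 0. The Visit IV and Visit VI texts agree: they fall 3 and 9 months after the start of treat-to-target together with the oral agent. No text delays the first capsule beyond the baseline visit.

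**Step 2. Lead of treat-to-target over the study drug.**

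| Version | Treat-to-target starts | Study drug starts | Lead |
|---|---|---|---|
| Run-in (section 8a, Table 1, one trial design sentence) | between −3 and 0 months | month 0 | up to 3 months |
| Month 0 (Run-in Phase, Summary of Procedure, section 4f, Visits I and III) | month 0, after the blood draw | month 0 | 0 months |

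**Step 3. What survives under each version.**

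| Statement | Run-in version | Month-0 version |
|---|---|---|
| Section 8a: not started together, time on the regimen first | holds | fails |
| Summary of Procedure and Visit III: start at the end of the run-in | fails | holds |
| Secondary Aim 1: run-in is standard aspart and detemir therapy | fails | holds |
| H1D: −3 and 0 months both reflect standard treatment | fails at month 0 | holds |
| Primary comparison: month-0 HbA1c precedes study drug in both arms | holds | holds |

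No single start time satisfies the first four rows together. The last row holds throughout.

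**Step 4. Could the run-in statements mean teaching only?** Table 1 has a separate row for instructions on the regimen, so the implementation row cannot simply mean instruction. Section 8a speaks of initiating the regimen as well as familiarizing patients with it. And if only teaching were meant, treat-to-target would start at month 0, which returns us to a lead of 0 months and leaves the assurance untrue.

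**The case against.** The best defence is that section 8a is loosely worded. The same section mentions a run-in session to familiarize families with titration, and far more of the text describes a month-0 start than a run-in start. On that view the intended schedule is recognizable and only three places are out of line. This narrows the repair but does not remove the problem, because one of the three is the safety assurance itself.

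The hypoglycemia plan also does not rest on staggering alone. The protocol provides twice-weekly calls in the first month, meter downloads every third day, 3 AM checks after basal changes, a bedtime threshold and a call-in rule for the first week of treat-to-target. These limit the practical consequence. They do not make the statement true.

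Four stronger readings are tempting, and the document does not support them:

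- **A reader might infer that the insulin regimen of the run-in is undefined.** It is defined: 1:1 conversion to detemir, equal basal and bolus shares, a preset carbohydrate ratio, log review in the first two weeks and a visit at one month. It is defined and then contradicted.
- **A reader might infer that a run-in start leaves H1D with no contrast, so that it must be withdrawn.** H1D also uses the −3 month HbA1c, which would still precede titration. A before-after contrast remains, but it compares prior care with treat-to-target.
- **A reader might infer that the main result is compromised.** Both arms have the same insulin regimen and a pre-drug month-0 HbA1c under either version, so the randomized comparison stands. The assumed 1.5-point effect is for metformin added to treat-to-target whichever timing applies. The document gives no figure for how timing would change the room left for metformin.
- **A reader might infer that every participant starts both interventions on one day.** The text supports a start from the same visit. It does not state the day of the first capsule.

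**Conclusion.** The contradiction is real and should be corrected. It concerns the first 3 of each participant's 12 months and applies to everyone who enters the run-in, including all 74 planned to be randomized. Under the visit procedures, the section 8a assurance is untrue. Under Table 1, the same-insulin contrast of Secondary Aim 1 is lost, and the month-0 half of the H1D reference already reflects titration.

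The case for correction rests on the inaccurate risk statement, on instructions that cannot both be followed, and on a secondary aim whose meaning depends on the answer. It does not rest on any damage to the randomized metformin-placebo comparison, which is intact. The conclusion assumes that study drug begins from the baseline visit, as the supply schedule and the follow-up visit texts indicate. Which start time is right is a clinical decision and is not judged here.

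**What to change.** The study team should:

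1. Choose one start time for treat-to-target and make these agree with it: the implementation row of Table 1, the Run-in Phase and trial design text, the Summary of Procedure and the run-in item after it, the Protocol paragraph of section 4f, the procedures for Visits I to III, and section 8a.
2. Rewrite the section 8a statements on staggering so that they describe what is actually done.
3. State what the month-0 HbA1c represents, and define the reference period for Secondary Aim 1 and H1D accordingly. If titration starts at month 0, both the −3 and 0 month values can serve as written. If it starts in the run-in, only the −3 month value precedes it. The contrast should then be described as prior care versus treat-to-target, and Secondary Aim 1 reworded.
4. Make sure the −3 month HbA1c that H1D uses is listed. The screening tests named for Visit I do not include it.

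The cost is one protocol amendment to existing text, with ethics board review of the corrected risk statement. The reconciliation itself needs no new procedure and no change to the sample size or the primary analysis.
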